#### Exploratory efficacy

3.8.3

Exploratory efficacy evaluation is based on the chemotherapy completion rate and NCS. The chemotherapy completion rate is used for patients enrolled in clinical studies where chemotherapy is in progress and is calculated as follows: chemotherapy completion rate = number of chemotherapy sessions completed after research project/chemotherapy sessions planned in the future∗100. The time point of investigating the chemotherapy completion rate is when all scheduled chemotherapy schedules are completed. NCS is performed as a statistical selective test and is conducted in 1 to 2 of 10 patients. The visit-window of the NCS that should be performed during the baseline visit will be ± 4 days.

#### Safety and adverse events monitoring

3.8.4

Safety assessment includes:

1.basic physical examination, vital signs, and electrocardiogram;2.examination of the presence of adverse reactions;3.clinical laboratory testing; and4.neurological tests.

The sub-investigator will record the details of any adverse reactions and use of concomitant medications during the clinical trial in the case report form. In case of an adverse reaction, the symptoms and signs of the adverse reaction, duration (start date/end date), severity, result, significance, causal relationship with the clinical investigational drug, and measures taken for its alleviation will be recorded. The names, dosages, duration of administration, reason for administration, etc, of the concomitant medications will be recorded in detail.

Clinical laboratory tests will be performed at visits 1, 2, 3, and 4. Since this study will evaluate the efficacy and stability of the combination of pregabalin, EA, and, CMT, it differs from clinical studies evaluating the safety and pharmacokinetic properties of drugs. Therefore, this study conducts clinical laboratory tests for the following items for the purpose of the standard safety lab test:

1.hematology: hemoglobin, hematocrit, red blood cell count, white blood cell count and differential count, platelet count;2.serum chemistry: glucose, aspartate aminotransferase (AST), alanine aminotransferase (ALT), alkaline phosphatase, creatinine phosphokinase (CPK), uric acid, total bilirubin, blood urea nitrogen (BUN), electrolytes (sodium, potassium, chloride, calcium, phosphorus), total protein, albumin, serum creatinine (SCr);3.coagulation: prothrombin time, activated partial thromboplastin time (aPTT);4.urinanalysis: pH, protein (albumin), glucose, leukocyte esterase, blood;5.pregnancy test (for women of childbearing age)

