The present study aims to verify the safety and efficacy of the concurrent use of EA or Chuna manual therapy (CMT) (a manual medicine treatment widely used in Korea) with pregabalin for patients with CIPN (especially, taxane-induced peripheral neuropathy in breast cancer and oxaliplatin-induced peripheral neuropathy in colorectal cancer), compared to pregabalin therapy alone. We hope that this study will validate the efficacy and safety of combination therapy and suggest a new approach for the treatment of CIPN.

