## Objective

2

The study aims to verify the hypothesis that the concurrent use of CMT or acupuncture treatment with pregabalin, a medication commonly used for CIPN is more effective and safe for the relief of CIPN symptoms than is pregabalin-alone therapy.

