The pregabalin used in this study is not a clinical investigational product and does not require allocation concealment, since it is administered to all groups. Moreover, it is impossible to blind the investigator and the participant in each group due to the nature of the study intervention, which is based on the contact between the patient and the medical staff. Instead, the investigator maintains blinding to prevent bias in evaluating the participant. If the clinical trial is completed, all clinical report forms (CRFs) are collected, the database process is terminated, and unblinding will be performed, if required for statistical analysis. Moreover, if it is deemed necessary to confirm the subject group due to an emergency situation during the clinical trial, the randomization code will be disclosed only to the participant, according to the principal investigator's discretion. If it is not possible to consult with the principal investigator and the situation is urgent, the randomization code of the subject will be disclosed after consultation with the randomization code officer. If unblinding is performed, the documentation of the reason for the unblinding will be retained and the participant with the disclosed randomization code will not be able to continue the trial.

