### Statistical analysis

3.9

All statistical analyses will be conducted by a blinded professional statistician. All participants who provided written consent and were assigned a screening number for the study are included in the screening set, and patients randomized to the treatment group are included in the randomized set. Intention-to-treat (ITT) analysis will be performed in patients who have received at least one pregabalin trial or at least one session of acupuncture or CMT. Per-Protocol Set (PPS) analysis will be performed in patients who meet the inclusion/exclusion criteria, have no significant conditions affecting the efficacy assessment, show > 80% treatment compliance, and have performed at least one evaluation after the baseline evaluation.

The statistical analysis for the efficacy evaluation, based on ITT analysis and PPS analysis are conducted in parallel. All statistical tests will be performed as two-sided tests with a significance level of 5%, and two-sided 95% confidence intervals. Primary outcome assessments are performed with ANOVA analysis to test the differences between the groups for changes in FACT/GOG-NTX at the end of week 5, compared to baseline. If the differences between groups are significant, the Tukey method will be used. For secondary outcome evaluation, continuous variables are analyzed with ANOVA analysis or Kruskal–Wallis test, and categorical variables are analyzed with Pearson's chi-squares test or Fisher's exact test. The Exploratory Efficacy assessment will summarize the descriptive statistics on the chemotherapy completion rate, followed by the appropriate statistical analysis.

For the occurrence of adverse events, the number of cases, number of participants, severity, and causal relationship with the investigational drug can be statistically analyzed by group, and nonparametric methods can be applied as needed. The results of vital signs, physical examination, electrocardiograms, and laboratory tests will be reviewed in a comprehensive manner, and statistical analysis will be conducted as necessary for the test items deemed clinically significant by the investigators. Depending on the nature of the data, continuous data will be summarized by observed values, mean, standard deviation, median, minimum, and maximum for each visit, and categorical variables will be summarized by frequency and percentage.

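### Adverse-event causality is assessed only against an investigational drug, so no event can be attributed to electroacupuncture or Chuna manual therapy, the treatments under test

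*Protocol article*

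**What the plan says.** Causality of adverse events appears in two places in the protocol article, and each names a drug only.

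- **3.8.4 Safety and adverse events monitoring:** among the details to be noted for each reaction, the "causal relationship with the clinical investigational drug, and measures taken for its alleviation will be recorded".
- **3.9 Statistical analysis:** besides counts of events and of affected participants, "severity, and causal relationship with the investigational drug can be statistically analyzed by group".

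Other sections bear on what that term can mean.

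- **3.6 Recruitment, randomization, blinding and non-blinding:** "The pregabalin used in this study is not a clinical investigational product". The same sentence says that concealment is unnecessary "since it is administered to all groups".
- **Section 2 Objective:** the hypothesis is that adding CMT or acupuncture to pregabalin "is more effective and safe for the relief of CIPN symptoms than is pregabalin-alone therapy". The Introduction also gives the safety of adding EA or CMT as an aim.
- **3.8.4, on what is captured:** "The sub-investigator will record the details of any adverse reactions and use of concomitant medications during the clinical trial". This is not restricted to drug reactions.

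**The concern.** A causality item is useful when it points at the treatment in question. Here the trial asks what EA or CMT adds to pregabalin, yet the only causal judgement described concerns a drug. The single drug in the design is common to all arms, and the article itself denies it investigational status.

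The article expects that the procedures can do harm. Section 3.4.3 avoids one manual technique in breast cancer patients because it might irritate the affected area, and 3.5.2 excludes patients with skin lesions or fractures that would interfere with EA or CMT. An event of that kind has no stated place in the causality item.

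What is at stake is the meaning of any treatment-related summary by arm, and the chance to collect these judgements at the time of the event. They are hard to reconstruct reliably afterwards.

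**Working it through.** The plan states no figure on this point, so there is none to reproduce. The check is mainly a comparison of sections.

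**Step 1: what can the drug term refer to?**

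| Candidate | A drug? | Investigational product according to the article? | Differs between arms? |
|---|---|---|---|
| Pregabalin | Yes | No (3.6) | No, given to all (3.6) |
| EA | No, a procedure (3.4.2) | Not stated | Yes |
| CMT | No, a procedure (3.4.3) | Not stated | Yes |

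Read literally, the term fits none of the three. Read generously, it means pregabalin, the one treatment that does not separate the arms. Neither reading gives attribution to EA or CMT.

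**Step 2: what is still collected and compared?** Section 3.8.4 records all adverse reactions with symptoms, dates, severity and result. Section 3.9 allows numbers of events, numbers of participants and severity to be analysed by group. Since pregabalin is common to all arms, an excess in the EA or CMT arm over pregabalin alone is direct randomised evidence on the added treatment. So capture and the between-group comparison are intact. Event-level attribution is what is missing.

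**Step 3: who is affected?** With 30 per group (3.3), the two procedure arms hold 30 + 30 = 60 of 90 participants. Planned sessions per patient are 3 × 2 + 2 × 3 = 12 for EA (3.4.2) and 2 × 2 + 1 × 3 = 7 for CMT (3.4.3). At full attendance that is 30 × 12 = 360 EA and 30 × 7 = 210 CMT sessions.

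**Step 4: would counts by arm make attribution redundant?** The document gives no adverse-event rates, so the rates below are assumptions. For two arms of n each, with p̄ the mean of p1 and p2, approximate two-sided 5% power is

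Φ{ [ |p2 − p1| − 1.96 √(2p̄(1 − p̄)/n) ] / √([p1(1 − p1) + p2(1 − p2)]/n) }.

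Example with 5% against 15% and n = 30: p̄ = 0.10; 1.96 × √(0.18/30) = 0.152; √(0.175/30) = 0.0764; (0.100 − 0.152)/0.0764 = −0.68; power about 25%.

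| Assumed rates | n = 30 | n = 24 (30 × 0.80, the 20% dropout in 3.3) |
|---|---|---|
| 5% vs 15% | 25% | 21% |
| 5% vs 20% | 42% | 35% |
| 10% vs 30% | 49% | 41% |

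The normal approximation is rough at such small counts, but the message is clear. The comparison by arm addresses the objective and is weak for uncommon procedure-related harms. Attribution is therefore a worthwhile supplement. The weakness comes from the pilot sample size, not from the causality wording.

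**The case against.** The strongest reply is that the safety objective is comparative and needs no causality judgement. All reactions are recorded, counts and severity can be set side by side by randomised group, and with pregabalin in every arm the difference estimates the harm of the added procedure. Investigator causality is subjective, and more so in an open-label trial. This stands. A reader might infer from the drug-only wording that the safety objective is missed, or that harms of EA and CMT cannot be separated from those of pregabalin. The documents do not support either conclusion.

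A second reply is that the term is template language for the trial treatments in general. Section 3.8.5 uses it just as loosely, listing exercise and physiotherapy among things that could affect the investigational drug, and the consent text in 3.2 speaks of reactions to the trial's interventions. That is plausible and argues against a deliberate decision to ignore procedural harms. It does not repair the two sentences that fix what is recorded and analysed. It also shows that suitable wording was at hand.

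Third, the article condenses a full protocol, and the case report form is not shown. Separate causality items may exist there. This also stands: the point concerns the wording in the article, and nothing shows that a needle-related event would in practice be coded as unrelated or assigned to pregabalin.

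Finally, a reader might size the problem by the upper limit after zero events, 1 − 0.05^(1/n), which is 9.5% for n = 30 and 11.7% for n = 24 (one-sided 95%). Those limits depend only on n and would be the same under any wording, so they do not measure this defect.

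**Conclusion.** The point holds as a defect of stated wording. In both places where causality is described it is tied to a term that fits no study treatment, or at best fits the one shared by all arms. Followed literally, the plan yields no event-level attribution to EA or CMT for the 60 participants who would receive them, and a related-event table would describe the wrong treatment or none.

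The consequence is limited. Capture of adverse reactions and their comparison by randomised group are unaffected, and no conclusion about the overall safety comparison follows from this wording. No numerical bias can be stated, because the article gives no event rates. The power figures illustrate only why attribution is worth having, and they rest on assumed rates. The conclusion also assumes that the full protocol and case report form carry the same wording. If they already assess each treatment separately, only the text needs aligning. It is still worth correcting, because the change is nearly free and the judgements are best made as events occur.

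**What to change.** In 3.8.4 and 3.9, and in the case report form if it uses the same wording, replace the reference to the investigational drug with a separate causality assessment for each study treatment the participant received: pregabalin, EA, CMT. Reconcile the terminology with the statement in 3.6 on pregabalin's status. Report EA-related and CMT-related events beside all-cause events by arm.

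Keep the all-cause comparison by arm as the main safety evidence. Judging whether an event is due to EA or CMT requires knowing that the participant received it, so the attribution will be unblinded and subjective. Rates per session and exact confidence intervals are optional.

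The cost is one or two extra items on the form and one extra safety table. Treatment, visits and sample size do not change.

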#### Early termination or dropout

3.8.5

The early termination or dropout criteria are as follows:

1.if the participant has been administered a drug that is expected to affect the safety or efficacy of the investigational drug including neuropathic pain medications; antiepileptics and antidepressants, excluding pregabalin (concomitant treatment with selective serotonin reuptake inhibitors [SSRI] and tricyclic antidepressants [TCA] is allowed only when the antidepressants are used in stable administration conditions, without change in the type, dose, and usage from 14 days before the run-in period); herbal therapies besides those included in the present study, which may affect the outcome of this clinical trial; exercise therapy; physiotherapy; anti-anxiety agents; sleeping pills (all sleeping pills other than triazolam, zopiclone, and zolpidem tartrate); anti-anxiety agents; analgesics; muscle relaxants; steroids; cilostazol; prostaglandins and related drugs; local anesthetics; N-methyl-D-aspartate receptor (NMDA) antagonists; sodium channel blockers; central sympathetic neurosuppressants; vitamin B1 and/or B12 prescribed for peripheral neuropathic pain; drugs that may cause irreversible retinal degeneration; and other investigational drugs2.if the participant requests the discontinuation of clinical trial treatment or withdraws consent3.if a serious adverse event has occurred and the investigator determines that the trial cannot be continued4.if serious violations of the protocol, including inclusion/exclusion criteria, are newly discovered during clinical trials5.if treatment compliance is below 70% and6.if, for any other reason, the principal investigator/sub-investigator determines that the trial should be discontinued.

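### Section 3.8.5 makes prohibited co-treatment, a request to stop treatment and low compliance grounds for leaving the trial, so week-5 scores can be lost from patients whom the ITT set keeps

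*Protocol article*

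**What the plan says.** Section 3.8.5 (Early termination or dropout) has six criteria.

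- Item 1 covers a long list of co-treatments, including "neuropathic pain medications; antiepileptics and antidepressants, excluding pregabalin", and also physiotherapy, exercise therapy and analgesics.
- Item 2 applies "if the participant requests the discontinuation of clinical trial treatment or withdraws consent".
- Item 3 applies after a serious adverse event when "the investigator determines that the trial cannot be continued".
- Item 4 covers serious protocol violations found during the trial.
- Item 5 applies "if treatment compliance is below 70" per cent.
- Item 6 applies when, for any other reason, "the principal investigator/sub-investigator determines that the trial should be discontinued".

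Section 3.9 (Statistical analysis) defines the ITT population as "patients who have received at least one pregabalin trial or at least one session of acupuncture or CMT", with no compliance condition. The primary ANOVA compares the groups on "changes in FACT/GOG-NTX at the end of week 5, compared to baseline". The per-protocol set, analysed in parallel, is limited to patients who "show > 80% treatment compliance", among other conditions.

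Section 3.2 (Study design) measures pregabalin compliance from doses planned, taken and returned at each visit. It measures EA and CMT compliance as sessions given against sessions planned.

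**The concern.** Stopping the allocated treatment and leaving the trial are different events, and section 3.8.5 does not separate them. Item 2 merges them outright. Items 3 and 6 speak of the trial, not of treatment. If patients who meet item 1, item 5 or the first half of item 2 are no longer assessed, the primary analysis lacks week-5 scores for people its own ITT definition includes.

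That loss need not be random. A patient whose neuropathy is not relieved is a likely candidate for another neuropathic-pain drug, an analgesic or physiotherapy. Treatment is open-label, so the tendency to seek other help may differ by arm. An analysis plan can choose how to handle scores that were never collected, but it cannot recover them.

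**Working it through.** **The plan's own figure.** Section 3.3 has 30 per group and allows 20% dropout: 30 × (1 − 0.20) = 24, which exceeds the roughly 20 per group of the earlier studies. The statement is correct, but it concerns numbers only, not who is lost.

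**Timing.** Visits 2, 3 and 4 fall about 2, 4 and 7 weeks after screening (section 3.2). Visit 3 is therefore 4 − 2 = 2 weeks after baseline, and visit 4 is 7 − 2 = 5 weeks after it. The primary score is due at visit 4.

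**Item 1.** No timing is attached, so it can apply on any day before visit 4. The document gives nothing from which to compute how often.

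**Item 5, pregabalin.** Tablet accounting at visit 3 can show low compliance three weeks before the primary assessment. This route exists in all three arms.

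**Item 5, sessions** (schedules from sections 3.4.2 and 3.4.3).

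- EA: 3×2 + 2×3 = 12 sessions, 10 of them due by the end of week 4. Since 8/12 = 66.7% fails and 9/12 = 75% passes, the criterion needs 4 or more missed.
- CMT: 2×2 + 1×3 = 7 sessions, 6 of them due by the end of week 4. Since 4/7 = 57.1% fails and 5/7 = 71.4% passes, it needs 3 or more missed.

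With independent misses (an assumption), binomial probabilities are:

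| Assumed miss rate | 5% | 10% | 15% | 20% |
|---|---|---|---|---|
| EA, whole course, P(≥4 of 12) | 0.2% | 2.6% | 9.2% | 20.5% |
| CMT, whole course, P(≥3 of 7) | 0.4% | 2.6% | 7.4% | 14.8% |
| EA, certain by end of week 4, P(≥4 of 10) | 0.1% | 1.3% | 5.0% | 12.1% |
| CMT, certain by end of week 4, P(≥3 of 6) | 0.2% | 1.6% | 4.7% | 9.9% |
| EA, expected number of 30 by end of week 4 | 0.03 | 0.4 | 1.5 | 3.6 |
| CMT, expected number of 30 by end of week 4 | 0.07 | 0.5 | 1.4 | 3.0 |

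Measured against the full course, then, the session route costs few week-5 scores unless attendance is poor.

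**What the 70% rule adds to the per-protocol set.** Compliance above 80% means at least 10/12 EA sessions (83.3%) or 6/7 CMT sessions (85.7%). Anyone below 70% is already outside that set, so for the efficacy analyses the termination rule bears only on ITT.

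**What outcome-related loss could do.** This is an illustration for item 1; every input is assumed. If a fraction q of an arm is lost and the tendency to drop out has correlation r with outcome, the mean of those remaining shifts by r·φ(z_q)/(1 − q) SD. Take losses of 20% in controls and 10% in a combination arm:

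- r = 0.3: 0.105 − 0.0585 = 0.046 SD
- r = 0.5: 0.175 − 0.0975 = 0.077 SD

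With 24 and 27 patients left, the standard error is √(1/24 + 1/27) = 0.281 SD, so the shifts are 17% and 28% of it. Swapping the split reverses the sign, and equal loss gives zero. The extra session measure in the EA and CMT arms would by itself push the other way, towards more loss in the combination arms.

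**The case against.** The strongest reply is that the loss is inferred. No sentence says that assessments stop, the list mixes treatment-level wording (item 2) with trial-level wording (items 3 and 6), and the article condenses a full protocol that may set out what happens after termination. This stands in part: a reader might conclude that the article orders follow-up to end, and it does not say so in terms. But the list is headed as dropout criteria and includes withdrawal of consent. Section 3.6 likewise bars a participant whose code is disclosed from continuing the trial. Leaving is therefore the ordinary reading of a rule that the article does state.

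A second reply is that the 70% rule is a weak example, because session compliance against the planned total is mostly settled when the week-5 score is due. That is right for EA and CMT sessions. The article also does not say that the 70% rule is applied at interim visits, so the pregabalin route is possible rather than certain. Item 1 is untouched by this reply.

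A third reply is that this is a pilot with 20% dropout already allowed, and that missing-data methods belong to an analysis plan not shown. The trial nevertheless runs a two-sided 5% efficacy test. The point here is the collection of scores, which the protocol governs, not the absence of an imputation method.

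**Conclusion.** The point holds as a fault in a stated rule: applied as worded, section 3.8.5 can remove week-5 scores from patients whom section 3.9 counts as ITT. It rests on reading early termination or dropout as leaving the trial, so confidence is medium. Item 1 carries most of the weight, item 5 matters mainly through pregabalin compliance, and the session-based part is small at ordinary attendance.

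A reader might infer that the rule will bias the trial in favour of the combination arms, or against them. The document supports neither. It gives no rates by arm and no link between dropout and outcome, and the plausible mechanisms pull in different directions. The shift of 0.05 to 0.08 SD in the illustration shows only what one invented split would do. The concern does not invalidate the trial; it identifies an avoidable loss that is cheap to prevent.

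**What to change.** State in section 3.8.5 that items 1 and 5, and a request under item 2 to stop treatment only, end trial treatment but not follow-up. These participants, like those stopped under items 3, 4 and 6 when able and willing, still complete FACT/GOG-Ntx, QLQ-CIPN20 and QLQ-C30 at visits 4 and 5 and are analysed in their randomised arm. Only withdrawal of consent to follow-up, or inability to be assessed, ends data collection. Low compliance is left to the existing per-protocol threshold of more than 80%.

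The cost is a wording change and a few more questionnaires at visits already scheduled; the primary one is self-administered. The ITT contrast will then include patients who took other treatments, and the parallel per-protocol analysis gives the view restricted to compliant patients.
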